### Statistical analyses

Primary outcome measures include [1] treatment outcome (i.e., abstinence rates) after a six-week intervention phase compared with baseline; [2] improvement in cognition and thus changes in neural measures of response inhibition, working memory and salience network connectivity in relation to craving, perceived stress and treatment success. After preprocessing, including movement correction and normalization to the Montreal Neurological Institute template, the echo planar images will undergo spatial smoothing with a Gaussian kernel of 8 mm full width at half maximum. The analysis will be conducted at both the single-subject and group levels via the general linear model approach. For resting-state analysis, the seed region is the right anterior insula for the salience network, which is one of the two core regions anchoring the salience network [95]. At the second level of analysis, paired t tests will be used to observe the effects of groups and time (preintervention vs. postintervention within one group). Additionally, full factorial models will be employed. Regression models incorporating various clinical variables, such as the severity of TUD, will also be calculated. Correction for statistical testing will be performed via familywise error correction at the level of *P* < 0.05. EEG data during sleep will be analysed via an in-house script in python, resulting in hypnograms and information, such as the timing and length of sleep stages, as well as spectrograms, including information on activation and frequency at specific electrodes.

SPSS (Statistics for Windows, IBM Corp., Armonk, NY) and R (R: A language and environment for statistical computing. R Foundation for Statistical Computing, Vienna, Austria) will be utilized to analyse physiological (e.g., heat rate during HIIT), psychometric (e.g., questionnaire data) and neuropsychological data. Multivariate analyses of variances with repeated measures will be conducted to analyse the dependent variables. Additionally, linear regression models will be employed to examine the influence of confounding variables on changes in the dependent variables. Finally, Cox regression analyses, such as examining brain activation in the dorsolateral prefrontal and/or inferior frontal regions during inhibition, will be performed to evaluate associations with possible relapse.

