**Methods:**

The study will enrol 140 treatment-seeking smokers aged 18–65 years who meet the DSM-5 criteria for TUD. The participants will be randomly assigned to four groups: CRT + HIIT in the morning, CRT + HIIT in the evening, HIIT alone in the morning, and HIIT alone in the evening. Assessments will be conducted at baseline (T1), postintervention (T2), and at a three-month follow-up (T3) at the Central Institute of Mental Health in Mannheim, Germany. The primary outcomes include abstinence days or amount of alcohol consumed in cases of relapse, as well as craving reduction. Secondary outcomes include improvements in cognitive functions (working memory, response inhibition, and cognitive control), measured through neuropsychological tasks, functional magnetic resonance imaging (fMRI), polysomnography, and self-report questionnaires. The repeated-measures design allows for within-subject comparisons to evaluate intervention effectiveness.

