### Hypotheses

Primary hypotheses and treatment outcomes:

A combination of CRT + sleep enhancement (i.e., CRT + HIIT early evening) as a six-week add-on therapy enhances treatment outcomes (i.e., relapse and craving) in smokers in comparison to CRT (i.e., CRT + HIIT morning) or sleep enhancement (i.e., no CRT + HIIT early evening) alone.The changes in neural measures of response inhibition, working memory and network connectivity in the salience network following the six-week treatment from baseline will be associated with self-reported craving and perceived stress, as well as treatment outcomes.

2.Secondary hypotheses and mechanisms:

Improvement in cognitive function in smokers.

c.CRT, as a six-week add-on training, improves cognitive function in smokers (i.e., CRT + HIIT in the morning versus HIIT in the morning).

d.Sleep enhancement (induced by HIIT in the evening) as a six-week add-on training improves cognitive function in smokers (i.e., HIIT in the evening versus HIIT in the morning).e.The combined effect of sleep enhancement and CRT (i.e., the interaction effect of CRT × sleep enhancement) increases cognitive function even further.

Improvement in neuronal abnormalities.

f.CRT alleviates neural dysfunction during cognitive performance in smokers (i.e., CRT + HIIT in the morning versus HIIT in the morning).g.Sleep enhancement as a six-week add-on therapy ameliorates neural dysfunction during cognitive performance in smokers (i.e., HIIT in the evening versus HIIT in the morning), as reflected by neural measures of response inhibition, working memory and connectivity strength within the salience network.h.The combined effect of both training methods is even greater (i.e., the effect of CRT + HIIT in the evening versus HIIT in the morning).i.CRT as well as sleep enhancement (i.e., HIIT in the early evening) as a six-week add-on therapy reduces connectivity strength in the salience network.

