## Discussion

Owing to the challenges faced by patients with TUD in maintaining abstinence, smoking remains a global health crisis and a leading cause of premature death [96]. This study aims to establish a therapeutic approach for improved treatment outcomes, including increased abstinence. Additionally, we aim to address this research gap by evaluating different intervention approaches to understand the imbalance between habitual and goal-directed behavior. Emerging evidence indicates an imbalance in habitual and goal-directed behavior among treatment-seeking smokers at both the neural and behavioral levels, suggesting that this imbalance can predict future relapses [65]. To achieve better treatment outcomes and assist treatment-seeking smokers in reaching their goals, we will implement two interventions in addition to the standard SCP. A notable aspect of our study is the implementation of outpatient HIIT and CRT, which has not been conducted in patients with TUD in previous studies. The outpatient setting allows participants to engage in the interventions individually within their familiar environment. As a contribution to the field, we aim to identify the mechanisms through which sleep enhancement and CRT may improve cognitive control, addressing a research gap regarding the neural mechanisms underlying the influence of cognitive control on abstinence. We hypothesise that the additional interventions will have differential beneficial effects on relapse rates and nicotine consumption by enhancing cognitive function. By utilizing our validated cognitive battery in the CRT intervention, we aim to enhance cognitive functioning in domains such as inhibition, working memory, attention, and decision-making. We anticipate further improvements in cognitive functions through the enhancement of sleep quality provided by early evening HIIT sessions. The use of a repeated-measures design can be considered a methodological strength, as it reduces error variance by allowing each patient to serve as their own control. This design will help to accurately assess the effectiveness of the interventions [97].

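### The fMRI plan assigns group effects to pre-post t tests within one arm, which show change over time only, and no between-arm contrast is named as the deciding test

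*Protocol article*

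**What the plan says.** All places are in the protocol article.

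- **Statistical analyses, imaging part.** At the second level, "paired t tests will be used to observe the effects of groups and time (preintervention vs. postintervention within one group". The next sentence is "Additionally, full factorial models will be employed". Its factors and contrasts are not given.
- **Statistical analyses, primary outcomes.** The first is treatment outcome, defined as "abstinence rates) after a six-week intervention phase compared with baseline". The second includes changes in neural measures of response inhibition, working memory and salience network connectivity, in relation to craving, stress and treatment success.
- **Statistical analyses, second paragraph.** For physiological, psychometric and neuropsychological data, "Multivariate analyses of variances with repeated measures will be conducted to analyse the dependent variables".
- **Hypotheses.** The first primary hypothesis compares the evening combination with two other arms. Hypothesis f reads "CRT alleviates neural dysfunction during cognitive performance in smokers (i.e., CRT + HIIT in the morning versus HIIT in the morning" and hypothesis g reads "ameliorates neural dysfunction during cognitive performance in smokers (i.e., HIIT in the evening versus HIIT in the morning". Hypothesis h also compares two arms, and e is a CRT by sleep-enhancement interaction. Hypothesis i, on connectivity strength, names no comparator.
- **Abstract, Methods.** "The repeated-measures design allows for within-subject comparisons to evaluate intervention effectiveness".
- **Discussion.** The repeated-measures design "reduces error variance by allowing each patient to serve as their own control", and is said to help in assessing effectiveness accurately.

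**The concern.** The effects in question are those of CRT and of training time. No participant receives more than one arm, so nobody serves as their own control for either factor. Only a comparison between randomised arms can isolate them.

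All four arms receive the cessation programme and HIIT, and all repeat the scans. All enter as treatment-seeking smokers, so abstinence can be expected to rise from baseline in every arm whatever CRT or timing does. A within-arm change carries all of this. Read literally, the imaging sentence would let an analyst report a group effect because one arm changed, or because one arm passed 5% and another did not, when the arms do not differ. The neural measures concerned are listed among the primary outcomes.

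**Working it through.** **1. The plan's own figure.** Sample size gives 128 participants (4 × 32), f = 0.25, 5% alpha and 80% power in an ANOVA on abstinence days at day 42. With noncentrality λ = N·f² = 128 × 0.0625 = 8 and 1 and 124 degrees of freedom, power is 0.801, and 128 is the smallest N that reaches 0.80. The figure therefore reproduces as a one-degree-of-freedom between-arm effect in the 2 × 2 layout. (With three numerator degrees of freedom, power would be 0.639.) The trial was sized for a between-arm comparison, not for a paired test.

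**2. What each test estimates.** Write the mean T1-to-T2 change in an arm as S + A. S is the change shared by all arms (cessation programme, HIIT, less smoking, repeat testing), and A is the effect of that arm's CRT and timing.

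- Paired test in one arm: estimates S + A and is significant whenever S is large enough, even if A = 0.
- Difference in change between two arms: (S + A₁) − (S + A₂) = A₁ − A₂. S cancels.

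The article reports no learning effects for the N-back task, which weakens the repeat-testing part of S for that task. The other parts remain.

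**3. Size, as an illustration.** The documents give no value for S, so a range is assumed, in SDs of the change score. Other inputs: n = 32 per arm (Sample size), two-sided 5%, a single measure without imaging correction, A = 0 in every arm, arms independent.

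- One arm significant: p from the noncentral t with 31 degrees of freedom and noncentrality S × √32.
- Two given arms disagree: 2p(1 − p).
- At least one of four significant: 1 − (1 − p)⁴.

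For S = 0.5: noncentrality 0.5 × √32 = 2.83, p = 0.782, 2 × 0.782 × 0.218 = 0.341, and 1 − 0.218⁴ = 0.998.

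| S (SD) | One arm significant | Two arms disagree | At least one of four |
|---|---|---|---|
| 0 | 0.050 | 0.095 | 0.185 |
| 0.2 | 0.195 | 0.314 | 0.580 |
| 0.3 | 0.376 | 0.469 | 0.849 |
| 0.35 | 0.483 | 0.499 | 0.929 |
| 0.5 | 0.782 | 0.341 | 0.998 |
| 0.8 | 0.992 | 0.015 | 1.000 |

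Disagreement cannot exceed 0.50, the value of 2p(1 − p) at p = 0.5, and it comes close to that near S = 0.35.

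**4. The between-arm test on the same data.** In 40,000 simulated trials at each of S = 0, 0.3, 0.5 and 0.8, the 2 × 2 test on change scores rejected in 0.049 of runs for CRT and 0.049 to 0.050 for CRT × timing. Timing has the same form as CRT by symmetry.

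**The case against.** The strongest reply is that the plan already contains suitable models and shows between-arm intent. The quoted sentence concerns second-level fMRI only. The sentence after it adds full factorial models, which can carry group and group × time effects. Repeated-measures MANOVA is named for the psychometric and neuropsychological data. The sample size rests on an ANOVA, and most treatment hypotheses name comparator arms. The baseline phrase in the first primary outcome names no test, and the error-variance remark in the Discussion is ordinary and true. A condensed article may also leave factors and contrasts to a fuller document.

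Most of this stands. A reader might infer that the paired tests alone decide whether CRT or timing works, that misattribution will follow, or that the trial gives up its randomisation. The documents support none of these. No sentence makes the paired tests decisive, and none proposes comparing one arm's p value with another's. Nor does every hypothesis contrast arms: i names no comparator, and the second primary hypothesis concerns associations.

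What the reply does not remove is the statement itself. The article assigns group effects to a test that has no group term. The factorial models come as an addition, with nothing to say that they take precedence. The wording is wrong whatever a fuller plan may contain.

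**Conclusion.** The point holds as an error in the stated analysis, of moderate severity. The within-arm paired tests cannot show effects of groups, and the article does not make the between-arm contrasts of its named factorial model decisive for hypotheses f to i. Framing abstinence against baseline is out of line with the first primary hypothesis and with the ANOVA behind the sample size.

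Under the assumptions in the table, for shared changes of 0.2 to 0.8 SD, a within-arm test is significant 20% to 99% of the time and two arms disagree 2% to 50% of the time with no CRT or timing effect. The between-arm test stays at 5%. These are not the trial's false-positive rates. The within-arm results detect a real change over time and become false claims only if that change is credited to CRT or timing. The article also applies familywise error correction to the imaging, so the figures would differ voxelwise. Correction would not turn a time effect into a group effect.

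**What to change.** 1. In Statistical analyses, state that the treatment hypotheses on neural measures are tested by the between-arm contrasts of the factorial model already named: group × time, or equivalently CRT, timing and CRT × timing on T2 minus T1. Tie these contrasts to hypotheses f to i, and give i a comparator.
2. Label within-arm paired t tests as descriptive of change over time, and remove the claim that they show effects of groups.
3. Reword the first primary outcome so that six-week abstinence is compared between arms.
4. In the Abstract and Discussion, say that effectiveness is judged by the randomised between-arm comparison. The remark on reduced error variance may stay.

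The cost is wording only: same data, software and sample. At N = 128 and f = 0.25 on the analysed scale, a one-degree-of-freedom between-arm effect keeps power of 0.80. A contrast of two single arms, 32 against 32, at the matching difference of 0.5 SD (2 × 0.25) has power of about 0.50. The choice between main effects and two-arm contrasts should therefore be made openly.

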A total of 128 participants will be randomized into four groups (4 × 32 smokers), receiving add-on interventions alongside a smoking cessation program (SCP) [50]. The randomization protocol will control for sex. Stratified (men/women) block randomization with permuted blocks of size 8 will be used. Groups 1 and 2 will receive CRT + HIIT either in the evening or morning, respectively. Group 3 and Group 4 will receive only HIIT in the evening or morning, respectively. Each subject will undergo three days of investigation. Assessments will occur before SCP (baseline, T1), after a six-week SCP (T2), and at a follow-up appointment three months later (T3). An in-house smartphone application will be used to remind participants about the exercises and to collect accompanying information, i.e., physical exertion (every training day), cigarette craving (3 times per week), and evaluation of the three interventions (three days per week). Instances of relapse and any sleep or physical problems can also be reported. These data will be stored on local servers at the institute, and no personal information will be collected. Between T2 and T3, biweekly telephone screenings will be conducted to assess abstinence or relapse, as well as the amount of cigarette consumption. See study schedule, Fig. 2.

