### Interventions

Standard Smoking Cessation Program (SCP): The SCP will consist of group treatment sessions conducted once a week for one hour over a duration of six weeks for each subject. The program is grounded in behavioral therapy principles and will be facilitated by a qualified therapist [53].

Cognitive remediation treatment (CRT): The CRT will be administered as an app-based, chess-focused battery of tasks to be completed twice a week over a period of six weeks, with each session lasting 60 min. The CB-CRT was initially applied as an in-person group training and has since been adapted into a German version compatible with the GYMCHESS^®^ app (https://gymchess.com). This treatment approach utilizes a validated battery aimed at enhancing cognitive functions, including short-term memory, selective and focal attention, pattern recognition, visuospatial abilities, planning skills, and inhibition [54, 55]. In addition to the freely available GYMCHESS^®^ version, the participants will use a modified version with a fixed selection of exercises so that the same cognitive domains will be trained and that training for all participants will take place twice a week. No personal data will be stored during the use of the application. The date and time when the exercises were performed are recorded. Additionally, the number of completed exercises, (in-) correct answers, as well as the difficulty of the task are recorded.

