The potential limitation of this study could be the high dropout rate, as it involves a variety of tasks and interventions. To mitigate this risk, participants will be adequately supported throughout the conduct of the story and motivated to complete the study. Additionally, the numerous tasks involved may present challenges in integrating the findings, although they also provide an opportunity to explore the complexity of TUD.

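### Repeated-measures MANOVA discards partly observed participants on three-visit outcomes, including craving, and gives a less precise change comparison on two-visit outcomes; a mixed model adjusted for T1 and sex would do better

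*Protocol article*

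**What the plan says.** **Method.** The Statistical analyses section says that SPSS and R "will be utilized to analyse physiological (e.g., heat rate during HIIT), psychometric (e.g., questionnaire data) and neuropsychological data", and then: "Multivariate analyses of variances with repeated measures will be conducted to analyse the dependent variables". It adds that "linear regression models will be employed to examine the influence of confounding variables on changes in the dependent variables". Cox regressions, for example on brain activation during inhibition, "will be performed to evaluate associations with possible relapse". No likelihood-based model for repeated measures is named.

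**Visits.** In Table 1 the smoking questionnaires, including the two craving scales (Questionnaire of Smoking Urges and Craving Automated Scale), are scheduled at T1, T2 and T3. The neuropsychological tasks that are repeated, the imaging and the polysomnography are scheduled at T1 and T2 only.

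**Status of craving.** The Abstract lists craving reduction among the primary outcomes, and the first primary hypothesis names craving beside relapse.

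**Dropout.** The Discussion says: "The potential limitation of this study could be the high dropout rate, as it involves a variety of tasks and interventions". The Sample size section adds three participants to each of four groups, taking 128 to 140.

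**Design features.** On allocation: "Stratified (men/women) block randomization with permuted blocks of size 8 will be used". On delivery of the cessation programme: "The SCP will consist of group treatment sessions conducted once a week for one hour over a duration of six weeks for each subject".

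**The concern.** Two features of the stated method work against the trial.

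1. Classical repeated-measures MANOVA needs every entered variable at every modelled visit. A participant who completes craving questionnaires at T1 and T2 but not at T3 contributes nothing to a three-visit model. The T2 value, taken directly after treatment, is thrown away. If people who relapse are more likely to stop responding (plausible, but not stated in the article), the complete cases are enriched for success. The comparison of arms could then be biased as well as less precise.

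2. With two visits, the group-by-time test compares mean changes between arms. Confounders are also handled on the change scale, in separate models. Neither description adjusts the arm comparison for the T1 value, which is collected on everyone and is usually the strongest predictor of T2.

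At stake are precision on most secondary outcomes, and both precision and possible bias on craving.

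**Working it through.** **Step 1. The plan's own figure.** Inputs from the Sample size section: f = 0.25, alpha 5%, ANOVA, four groups, N = 128, power 80%. The noncentral F has λ = f²N and denominator df = N − 4. The numerator df is not stated; 1 (a main effect or the interaction in the 2 × 2 layout) reproduces the figure:
- λ = 0.0625 × 128 = 8.0, denominator df 124, power 80.1%.

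**Step 2. The dropout allowance.** 4 × 3 = 12, and 12/140 = 8.6%. Check: 128/(1 − 12/140) = 140. Any loss above about 9% leaves fewer than 128 complete cases.

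**Step 3. What complete-case analysis would cost.** The article gives no loss rate, so 20% and 30% are assumptions.

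| Assumed loss | Complete cases of 140 | Discarded | λ | Power (f = 0.25, 1 df) |
|---|---|---|---|---|
| 8.6% | 128 | 12 | 8.0 | 80.1% |
| 20% | 112 | 28 | 7.0 | 74.6% |
| 30% | 98 | 42 | 6.125 | 68.8% |

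The f of 0.25 was set for days of abstinence at day 42. The last column therefore applies to that endpoint only if it is analysed on complete cases. For craving the article gives no effect size, so the table shows how many people are lost but not the resulting power.

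**Step 4. Where a mixed model regains participants.**
- *T1, T2 and T3 (most questionnaires, including craving):* someone with T2 but no T3, or T3 but no T2, is excluded from a three-visit MANOVA and kept by a likelihood-based model.
- *T1 and T2 only (for example the neuropsychological tasks):* T2 is the only post-baseline value. A participant without it is excluded under either method. The number regained is zero.

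**Step 5. Precision with two visits.** Take equal variances of 1 at T1 and T2 and correlation r (assumed; the article gives none).
- Change score: Var(T2 − T1) = 2(1 − r).
- Adjusted for T1: residual variance = 1 − r².
- Ratio: (1 − r²)/[2(1 − r)] = (1 + r)/2.

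| r | Change score | T1-adjusted | Ratio | Reduction |
|---|---|---|---|---|
| 0.3 | 1.40 | 0.91 | 0.65 | 35% |
| 0.5 | 1.00 | 0.75 | 0.75 | 25% |
| 0.7 | 0.60 | 0.51 | 0.85 | 15% |

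Below r = 0.5 the change score is noisier than the T2 value alone (variance 1). The Discussion's statement that repeated measures reduce error variance therefore does not hold for the arm comparison at such correlations.

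**Step 6. Therapy groups.** A variance inflation would need the group size, the intraclass correlation, and whether each group contains one arm or several. The article gives none of these, so no figure is offered.

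**The case against.** **The article names only a family of methods.** It is a condensed account, and model terms, analysis population and missing-data rules are commonly left to a full protocol or SAP. This stands for sex and therapy group. A reader might infer that the plan ignores its sex strata and treats members of a therapy group as independent, so that its standard errors are wrong. The text does not support that. It lists no model terms at all, the unnamed confounders could include sex, and the randomisation is said to control for sex. Omitting a balanced stratification factor mainly costs precision. Whether group delivery matters depends on nesting, which is not described. The objection does not reach the choice of method, which is stated.

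**Not every missed visit removes a participant.** This stands. Exclusion is the default behaviour of the classical method rather than a rule in the article, and it concerns only visits in the model. A missed T3 removes nobody from the two-visit outcomes.

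**The MANOVA may not govern abstinence.** This also stands. The sentence follows one limited to physiological, psychometric and neuropsychological data. The sized endpoint is a single day-42 count in an ANOVA. Relapse appears under Cox regression, which can censor dropouts, and follow-up abstinence is collected by telephone. It would be wrong to read 75% or 69% as the trial's power. Craving questionnaires, however, are psychometric data and fall within the sentence.

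**The trial does not predict high dropout.** Correct: it says this could be a limitation, attributes it to the number of tasks and interventions, and describes mitigation. That relapsers leave is an assumption of this review.

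**Change scores are valid under randomisation.** True; the loss is one of precision. If the T1 value were among the confounders, a regression on change would give the T1-adjusted contrast. But those regressions are described as examining confounders, not as the comparison of arms.

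**Conclusion.** The concern holds in a limited form. The article fixes a method that is prone to complete-case analysis and based on change, while naming high dropout as its potential limitation and allowing for 8.6% loss.

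- For three-visit questionnaires, including craving, the classical method discards partly observed participants: 28 of 140 if 20% lack a modelled visit, 42 if 30% do. Both rates are assumed.
- For two-visit outcomes the gain from changing the method is in precision only: 35%, 25% or 15% lower residual variance at an assumed r of 0.3, 0.5 or 0.7.
- Complete-case power of about 75% or 69% is an illustration under assumed losses. It concerns the sized abstinence endpoint only if that endpoint is analysed on complete cases.
- Nothing can be said about the size or direction of any effect of therapy grouping on the standard errors.

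The stated method is not invalid. A better one is available from data the trial already collects, so the change is worth making before analysis.

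**What to change.** Replace the MANOVA sentence by a linear mixed model, fitted by likelihood, on all randomised participants with any post-baseline value. Fixed terms: CRT, timing, CRT × timing, visit and their interactions with visit, the T1 value of the outcome, and sex as the stratification factor. With T2 as the only post-baseline visit this reduces to an analysis of covariance. Make this model the comparison of arms, and keep the regressions on confounders as supporting analyses.

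The model assumes that missingness depends only on observed values. It does not protect against dropout driven by unobserved relapse or craving, so its results should be described with that assumption.

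Record each participant's SCP group as a data field. State whether groups are formed within or across arms, and add a therapy-group term if that structure calls for it.

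State which method governs days of abstinence, so that the reach of the repeated-measures sentence is clear.

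Cost: analysis wording and one retained identifier. No new assessment, visit or participant is needed.
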